#### Overload and Progression

The main factor that modifies the demand of the task is water resistance. Aquatic physical therapy is based on several important bioengineering properties. The basic forces acting upon the patient while in the water consist of buoyancy, drag, and inertial forces. According to key hydrodynamic principles, a moving limb under water is acted on by drag and lift forces. Total drag can be defined as a resistant force opposite to the direction of movement of an object. The viscous properties of the water behind an object are referred to as form drag. The turbulence is generated by the mass of water that is sucked along behind an object in the form of retarding eddies and is proportional to the size and shape of the frontal area that is being pushed against the water. The relationship between the drag force and the velocity of the movement is nonlinear, so that the drag increases as a function of velocity squared (v^2^). Once the speed doubles, the consequent drag force quadruples. If the participant is in a head-out immersion, the buoyancy decreases his weight-bearing on the ground and by that his sensory input is reduced; this may increase the challenge on the balance control system, thus increasing overload. Furthermore, when the water is turbulent, it causes a continuous perturbation of posture during fix of support exercises and especially during exercise involving change of support (e.g., stepping, walking). Progressions will also be made by including open and closed eyes, stance width, single (level 3) and double leg support (level 2), standing on unstable support surface (such as a flat ball and noodles) during standing. Increased step speed will dramatically increase water resistance and a rapid extra step after the first step is challenging for power production (at all levels of training). Increasing the magnitude of the applied perturbations (e.g., pushes by the instructor and classmates) and applying it unexpectedly, and increasing the speed of forward and backward walking increases the load during gait and balancing.

#### Individualization

The balance training intervention is performed on five levels where each level reflects different increasing demands on the postural control system Training programs should be tailored to the individual needs and abilities of the participant [73]. This process requires interaction with an experienced therapist, instructor, or coach and should not be based on a "cookbook" approach to training. As in any type of training, for improvement to occur it is crucial to maintain a progressive and specific training load for each of the participants. Progressions should be made when the individuals have reached adaptation. On each level the instructor can instantly modify an exercise to be more or less challenging for each participant. For example, the instructor can increase the difficulty of a certain exercise by instructing a participant to use less external support, close the eyes, decrease the support area (stand on one leg, narrow the stance or on noodle, not use the arms to balance, move the head during the exercises, etc.) while another participant will not find this equally challenging. These "tools" allow the instructor to implement exercises on a group level that are still challenging for each individual, even if the skill level in the group varies. In addition, variability is important to keep subjects motivated and excited to pursue the training.

#### Generalizability

The goal of each session in the current program is to constantly challenge the postural control system with exercises that incorporate elements related to the demands of normal activities of daily living [74]. To promote generalizability, during the water-based and perturbation exercises the subjects perform a variety of real life dual tasks (cognitive and movement tasks).

#### Instructors

The program should be implemented by two instructors or physical therapists (and a life saver outside the pool) who, based on each individual subject's background and current skill/fitness level, can assess at what level a subject should begin the training program to maximize compliance and outcome and maintain safety. Any form of physical training, either learning and perfecting a sport skill or rehabilitating after an injury or disease, is a process that incorporates both physiological and psychological factors. These factors must harmonize on an individual level for the training process to be successful. A very important role of the instructor is to monitor the training process on an individual level and adapt the training program to optimize outcome and maximize performance. When needed, the instructor should be able to modify the execution of an exercise "on-the-fly" to customize the difficulty on an individual level. The instructor and the lifeguard are near by and fully alert to the security of each participant.

The instructors should be able to direct the subject's attention toward important aspects of the skill being learned to increase awareness. To enhance learning, subjects in this study are provided with instructions regarding the task goals. For example, subjects will be told to take steps as quickly and for as long as possible during balance perturbations or to avoid limb movements during upright stance counteracting water turbulence. These instructions will be gradually reduced as training progresses to avoid dependency [75]. During the training period there is little risk that a participant will fall. Although the participants will be pushed during the perturbation exercises, the water will keep the participant from falling on the pool floor and injuring him/herself in the most demanding levels of exercise. The risk should be minimal. At the beginning, exercises in level 5 will incorporate mild/gentle external balance perturbation exercises applied by the instructor. **It is important to note that these exercises will be customized to each subject's ability. They will be designed to be challenging but never dangerous**. The participants will be repeatedly instructed to ask for help if they feel uncomfortable about performing a certain exercise. Initially, the training will progress slowly to help everyone find their level of ability and not take any unnecessary risks. In fact, an important part of the training is to make each individual learn what their ability is. Overall, the training should be less dangerous than land-based exercises or other activities of daily living.

#### Improving gait and balance in Stroke survivors – Pilot Data

The following section describes findings from a pilot study conducted in collaboration between Ben-Gurion University and the hydrotherapy center in Shaa'r Ha-Negev using the training program presented here. A group of 8 participants (3 female, 5 male) between 71 and 85 years participated in the program two-times a week for 12 weeks. Compliance with the exercise program was excellent (88% average attendance over the 12-week program). Overall, functional status variables improved for all of the participants. Stroke survivors showed the largest improvement in Timed Up and Go (from 14.3 sec to 12.2 sec), and in Berg Balance Test (from 47.3 to 50.2).

## Methods/design

### Experimental protocol to assess the efficacy of the training program

A randomized controlled cross-over trial will be performed to assess the efficacy of the water-based training program that uses perturbation of balance to trigger automatic reflex-like postural responses as well as volitional stepping reactions. Ethical approval for this study was obtained from the Research Ethics Board of Soroka Medical Center and Ben-Gurion University Helsinki Committee (Trial registration number #NCT00708136).

### Recruitment of subjects

Community-dwelling older adults will be recruited from the community of the Sha'ar Hanegev council via advertisements in local newspapers, the internal brochure of the "Yahdav" elderly center and by personal contacts. The subjects who ambulate independently will be randomly allocated to either the water-based exercise group or the control group without intervention. A short interview examined whether the subjects met the inclusion-exclusion criteria. Participants were excluded if they had received physiotherapy or hydrotherapy, or attended community exercise classes in the past six months, had orthopedic surgery within the prior year; showed an indication of cognitive impairment (Mini-Mental Score <24 [76]), had severe focal muscle weakness or paralysis, serious visual impairment, severe peripheral or compression/entrapment neuropathies, any neurological disorders causing balance or motor problems, or cancer (metastases or under active treatment). Prior to their inclusion all subjects received medical clearance from their primary care physician to participate in the study.

### Intervention

The intervention program will last 12 weeks, with two 30-minute sessions per week (24 training sessions). This duration and intensity is similar to that used previous perturbation-based training studies [50,51,77,78]. All subjects will be asked to refrain from initiating any other new exercise programs, or otherwise consciously change their activity levels, during their participation in the study. For the perturbation-based training program, each session will consist of 2–5 minutes of warm up exercises, 15–20 minutes of water-based exercises including voluntary step training (see levels 1–4 exercises), about 5 minutes of perturbation training, and 2–5 minutes of cool-down exercises.

### Types of data to be obtained and measurement techniques

The following tests will be performed, for research purposes only, on all participants in the study. All outcome measures will be assessed before and after the training period.

#### Functional and objective balance tests

The following standardized functional tests will be administered.

1. Voluntary Step Execution Test[53,66,72]: This test will be performed on the portable Kistler 9287 force plate (Kistler Instrument Corp, Winterthur, Switzerland). Participants will be instructed to stand relaxed, view a target placed on a wall 3 m in front of them and to take a step as quickly as possible following a random somatosensory cue. Following a brief learning period, assessments will be made in three directions in random order (forward, backward, and sideways). The time from lifting of the foot (step start) to placing it on the ground will be measured using a portable force plate. The average of these measurements will represent the step execution time. Step execution will also be measured during performance of a secondary attention-demanding task, as described in details by Melzer and Oddsson [53,66,72] (Figure 4). Inter- and intra-rater reliability was good to excellent for the pooled population of young and elderly and for elderly only ((ICC(2,1) = 0.74–0.92 and 0.62–0.88, respectively) [72].

**Figure 4 F4:**
[figure not shown]
An example of forward step execution data for a 90-year-old subject during single (bottom) and dual (top) task conditions. Note that the tap cue is detectable in all of the signals. Note the differences in step reaction times between the two task conditions (distance between C and A). COPx = Mediolateral center of pressure, Fy = Ground reaction forces (shear forces) in antero-posterior direction. Fz = Vertical ground reaction forces, mm = millimeter, N = Newton. The following events are marked with vertical lines: Tap cue (C), Initial deviation of COPx (A), Foot-off (FO), Foot contact (FC).

The five primary outcome measures correspond to the specific aspects of voluntary step execution that were targeted in the water-based training program that include perturbation exercises. The following events were extracted from the ground reaction force data (cf. Figure): (1) The step initiation phase was detected from the tap cue (a spike in the shear ground reaction forces in the anterior-posterior direction (C in Figure) to the first medio-lateral deviation of the center of pressure (COP) towards the swing leg (COP excursion greater than 4 mm from baseline sway following the tap (A in Figure); (2) Foot-off (FO in Figure 4 was defined at the sudden change in the slope of COP towards the stance leg in the medio-lateral direction; (3) Foot-contact (FC in Figure 4) was defined as the onset of unloading the stance leg seen in the vertical ground reaction force; (4) Preparatory phase duration was calculated as the time from step initiation to foot-off; (5) The swing phase duration was calculated as the time from foot-off to foot-contact. The analysis of step execution data extracted specific temporal events using a program written in MatLab (Math Works Inc, Cambridge, MA, USA).

We have chosen the voluntary step execution test during single and dual task conditions to be measured since in a review published recently, Piirtola and Era [79] found that measures related to dynamic posturography (moving platforms) were not predictive of falls [79]. However Melzer et al. [53] found that application of the voluntary step execution test similar to the test in the proposed study identified elderly fallers.

2. Stabilogram-Diffusion Analysis: An automated algorithm will be used to extract standardized stabilogram-diffusion parameters from each of the COP data sets collected during quiet standing. These parameters include diffusion coefficients, critical displacement, critical time and scaling exponents for both lateral and anterior-posterior sway directions [80,81]. For each of the conditions (eyes open and eyes closed), participants will be required to stand on the platform 10 times with the eyes open and 10 times with the eyes closed for 30 s each. For each trial, they will be instructed to sway as little as possible.

A computerized automated procedure will be used to analyze the center of pressure recordings. Eighteen parameters (see below) will be extracted from the stabilogram-diffusion analysis to describe different aspects of the postural control process. These include two sets of the following parameters; one for medio-lateral and one for the anterior posterior direction and one resultant (refer to Figure 5 for a graphical illustration of the stabilogram-diffusion plot):

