### Statistical analysis

Normality will be ascertained by the Shapiro-Wilk statistic (non-significant) and normal Q-Q plots, indicating that parametric statistics are able to be used. A repeated measures analysis of variance for intervention * time will performed to determine if there are any differences in effect between the two exercise training circuits. The repeated measures of time are baseline, 3 months (post-intervention of the first group – 1^st ^circuit) and (6 months post-intervention of the second group – 2^nd ^circuit). The effects of training on the mean step reaction times (step initiation, time to foot-off, time to foot-contact, preparatory phase, and swing phase), postural stability measure (C_T_, C_D_, D_S_, D_L_, H_S_, H_L_), BBS, TUG, and LL-FDI scores will be calculated using SPSS (version 10.1, SPSS Corp., Chicago, IL). Order of intervention will be also analyzed as a covariate in order to detect any carryover effect from the previous intervention. If a difference between the two training circuits will be found for any variable, *post hoc *comparisons with Bonferroni adjustment will be made. Wilcoxon signed rank test and Mann-Whitney U-tests will be used in case the variable was not normally distributed. Results will be presented as mean values ± SD, the level considered to be statistically significant was *p *< 0.05.

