### Sample size estimate

A sample size requirement of 36 was estimated to detect an effect size of 0.8, powered at 80% and alpha of 5% was chosen for a clinically meaningful estimate. The estimation was performed two-sided. Based on a paper by Melzer et al. [53] the investigators found that step execution (average foot-contact times) during the execution of cognitive tasks were 1414 ms ± 417 for elderly fallers and 1165 ± 352 in elderly non-fallers. It was estimated that 32 subjects are required to detect a clinical change in this parameter. For the current study we have used an attrition rate of 10% (32 × 1.10 = 36).

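### Five primary step measures are each tested at 5% with nothing controlling error across them; if any one counts as success, the familywise error is about 13–19%

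*Protocol article*

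**What the plan says.** The text after Figure 4, under Functional and objective balance tests, declares the primary outcomes: "The five primary outcome measures correspond to the specific aspects of voluntary step execution that were targeted in the water-based training program". Statistical analysis lists them as "step initiation, time to foot-off, time to foot-contact, preparatory phase, and swing phase", in one sentence with the sway parameters, BBS, TUG and LL-FDI, and closes with a single threshold: "the level considered to be statistically significant was *p *< 0.05".

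The step test is done under two conditions. Item 1 of the balance tests says "Step execution will also be measured during performance of a secondary attention-demanding task", and the text after Figure 4 adds "We have chosen the voluntary step execution test during single and dual task conditions to be measured". Statistical analysis does not say whether the two conditions are tested separately, averaged or modelled together.

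Bonferroni appears once, for post hoc comparisons that follow a difference between the two training circuits in some variable. Sample size estimate uses an unadjusted two-sided 5% and one parameter: "step execution (average foot-contact times) during the execution of cognitive tasks". It does not call that parameter the primary outcome.

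**The concern.** Several primary outcomes can be legitimate if the plan ranks them, requires all of them to succeed, or divides the error among them. The article does none of these. It fixes five primaries and 5% for each, and places its only adjustment after the step where the primary error has already been spent. One significant step measure out of five could then be reported as a positive primary result, with a chance of error well above the 5% that the article presents. The trial's main efficacy claim, faster stepping, rests on these measures.

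**Working it through.** **Inputs from the article.** Five primary measures; 0.05 per test, two-sided; 32 participants before attrition, so 16 per arm. Preparatory phase runs from step initiation to foot-off, and swing phase from foot-off to foot-contact.

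**The plan's own figures.** The article states no familywise error rate, only 5% per test. Its attrition step reproduces: 32 × 1.10 = 35.2, rounded up to 36. The base figure of 32 does not follow from an effect size of 0.8 in a two-group comparison: 2 × (1.960 + 0.842)² / 0.8² = 24.5, or 25 per arm. That is a separate matter and does not bear on this point.

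**Independent tests, as a reference.** Familywise error = 1 − (1 − 0.05)^k.
- k = 5: 1 − 0.95⁵ = 0.226
- k = 10: 1 − 0.95¹⁰ = 0.401

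**Allowing for the overlap.** Write I, P and S for the initiation, preparatory and swing durations. If foot-off and foot-contact are timed from the tap cue, foot-off = I + P and foot-contact = I + P + S. Three durations then determine all five measures, so the tests are correlated and the error is below the independence figure.

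**Assumptions.** The article gives no correlations. I took −0.2 to 0.5 between phases, 0.3 to 0.8 between single and dual task, and both equal and unequal phase variances. Trials were simulated under no effect, with 16 per arm and two-sided two-sample t-tests. With equal phase variances, the chance of at least one p < 0.05 was:

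| Phase correlation | Five measures | Ten tests, task correlation 0.3 | Ten tests, task correlation 0.8 |
|---|---|---|---|
| −0.2 | 18% | 33% | 27% |
| 0 | 17–18% | 31% | 26% |
| 0.3 | 15% | 28% | 23% |
| 0.5 | 14% | 24% | 21% |

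Unequal variances lower these slightly, to 13% for five measures and 20% for ten tests. Separate runs of the same model, some with slightly different settings, agree. Across all runs the range is 13–19% for five measures and about 20–33% for ten tests.

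**Stronger correlation.** With one common correlation among five tests, the error is 18.4% at 0.5, 12.8% at 0.8 and 10.2% at 0.9. It stays above 5% unless the measures are practically identical.

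**Power if the error is divided.** The first Holm step over five measures is at 0.05/5 = 0.01. A test with 80% power at two-sided 0.05 has power Φ(1.960 + 0.842 − 2.576) = Φ(0.226) ≈ 59% at 0.01. For an effect size of 0.8 in two groups, n per arm rises from 25 to 37, since 2 × (2.576 + 0.842)² / 0.64 = 36.5.

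**The case against.** **A fuller analysis plan may contain a rule across outcomes.** It may. But the article does more than stay silent: it names five primaries, fixes the level and assigns its one adjustment elsewhere. Followed as written, it gives the wrong error rate.

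**A reader might infer ten primary tests and quote the upper figure of about 33% as the trial's error rate.** The documents do not support that. Both task conditions are measured, but Statistical analysis lists five mean times and does not say that the conditions are tested separately. The ten-test range is conditional.

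**A reader might take the clause about finding a difference in any variable as a rule for declaring success.** It is a trigger for post hoc comparisons. The article states no success rule at all, so the 13–19% depends on someone counting any one of the five as a positive result. Nothing in the text prevents that.

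**The scope of the Bonferroni step is not defined.** Comparisons within a variable are the likelier reading. On any reading the step follows a finding made at 0.05, so it does not protect that finding.

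**The figure counts errors in both directions.** This stands. A false claim that training speeds stepping is about 7–10% for the five measures, against a nominal 2.5%; the relative inflation is similar.

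**The simulation is not the planned analysis.** It uses two-sample t-tests, not the three-time-point repeated measures ANOVA of a cross-over. The inflation comes from the number and correlation of the tests, so this probably changes the rate little.

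**The arithmetic overlap among the five is not a further fault.** It brings the error below the 23% of independent tests.

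**Conclusion.** Wrong as written; should be fixed. Five unranked primary measures at 5% each, with no adjustment across them, give a two-sided familywise error of about 13–19% under no effect if any one is read as success. This rests on assumed phase correlations of −0.2 to 0.5. The error would be about 20–33% only if single- and dual-task results were tested separately, which the article leaves open. That the five measures are uncontrolled follows directly from the text; the exact size depends on correlations that the article does not give.

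**What to change.** In the text after Figure 4 and in Statistical analysis, adopt one of two equally valid forms:

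1. Name dual-task foot-contact time, the sample-size variable, as the single primary outcome. Make the other four step measures and all single-task results secondary.
2. Keep the five as primary and apply Holm across them, with ordered thresholds 0.05/5, 0.05/4, 0.05/3, 0.05/2 and 0.05.

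In either case, state how the single- and dual-task conditions enter the primary analysis. Under the second form, testing them separately would make the family ten, not five.

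Reconcile the definitions at the same time. Item 1 of the balance tests measures from foot lift to placement and calls the average step execution time; by the text after Figure 4, that interval is the swing phase. Sample size estimate equates step execution with foot-contact time, and Statistical analysis lists time to foot-contact separately from swing. The primary variable needs one definition, including its starting event.

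The cost is a few sentences in three sections, with no extra participants or measurements. Under the first form, the other phase measures can no longer carry a confirmatory claim alone. Under Holm, each test has less than the stated 80% power, about 59% at the first step for a test that had 80% at 0.05.

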**Discussion:**

This study will determine whether a water-based balance training program that includes perturbation exercises, in a group setting, can improve speed of voluntary stepping responses and improve balance control. Results will help guide the development of more cost-effective interventions that can prevent the occurrence of falls in the elderly.

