**Figure 5 F5:**
[figure not shown]
A schematic Stabilogram-Diffusion plot indicating the parameters that can be extracted to describe properties of the postural control process.

C_T _Critical Time, separates short-term and long-term regions. Indicates where the balance control system switches from an open-loop to a closed loop behavior.

C_D _Critical Displacement, indicates mean square displacement of the COP at the Critical Time. Indicator of short-term body sway that the subject is able to control.

D_S _Short-term diffusion coefficient, indicates the stochastic activity (frequency and amplitude) of the COP, the random walker, in the short-term region. Assessed from the slope of the stabilogram-diffusion plot in the short-term region.

D_L _Long-term diffusion coefficient, as D_S _for the long-term region.

H_S _Short-term scaling exponent, indicates the degree of correlation between past and future values of the COP. A value of 0.5 indicates a classical random walk (50% chance of COP displacement in one direction or the other); <0.5 indicates anti-persistence, i.e., the COP tends to come back to a certain equilibrium point (suggests closed-loop control); >0.5 indicates persistence, i.e., the COP tends to drift away (suggests open-loop control). Values can be between 0 and 1.

H_L _Long-term scaling exponent, as H_S _for the long-term region.

Stabilogram-diffusion parameters will be extracted for both eyes-open and eyes-closed conditions. The difference in critical displacement between eyes-open and eyes-closed will be used as an indicator of how much an individual relies on vision to control body sway. A large increase in sway with eyes closed would indicate visual reliance.

3. Berg Balance Scale[82]: The participant is scored on 14 tasks graded on a 0–4 scale to evaluate balance function under different conditions (maximum score 56). Wang et al. [83] found good internal consistency reliability (Cronbach's alpha = 0.77), good inter-rater reliability (ICC(2,1) = 0.87), and moderate correlation with the TUG and usual gait speed (Spearman's rho = -0.53 and 0.46, respectively).

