## Discussion

This study is the first to use water-based training that includes perturbation exercises and water turbulence in a group setting as an intervention to reverse age-related impairments in the ability to step quickly and recover from loss of balance. It differs from previous studies done in the water in this area in a number of significant ways. To date, no study has proposed using a water-based training program that includes perturbations to train stepping reactions and investigate the potential of water turbulence to improve stability. Only four exercise regimens have proposed the use of perturbations to improve stepping in elderly persons; all were land-based exercises regimens [49-51,89].

The water-based training program that includes perturbation exercises as outlined is targeted specifically to: 1) step execution-recovery reactions that are known to be impaired in older adults and associated with increased falling risk [53]; 2) the water-turbulence during voluntary exercises challenges balance control in multiple directions; 3) the perturbations are applied by instructors and classmates in predictable and unpredictable manners that allow subjects to exercise safely and progress when needed. Based on our previous findings [53,66], ongoing cognitive exercises are included to increase the load and specificity of training.

We hypothesize that the novel water-based balance training that includes perturbation exercises will improve balance control and increase speed of stepping, and this should help to reduce the incidence of falls. Due to the limitation of randomized controlled cross-over trials, the investigation of effects on falling is beyond the abilities of the present study. The results of the present study will add evidence regarding the effectiveness of perturbation-based balance training programs, and will be novel in conducting the perturbation exercises in water against water resistance and in a group setting that provides cost-effective exercise programs for long-term improvement followed by maintenance of the training benefits.

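### Improved balance control is a stated hypothesis, but its stabilogram test has up to 36 parameters, each at p<0.05, with no lead parameter and no adjustment across them

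*Protocol article*

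**What the plan says.** **Balance control as a question of the trial.** The abstract's Discussion says the study will determine whether the programme "can improve speed of voluntary stepping responses and improve balance control". The main Discussion hypothesises that training "will improve balance control and increase speed of stepping". The section Randomized Cross-Over Clinical Trial also gives stepping speed and balance control in upright stance as the purpose. The abstract's Methods/Design names two outcome measures: step reaction times, and postural stability by stabilogram-diffusion analysis.

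**The parameters.** Functional and objective balance tests, item 2, states: "Eighteen parameters (see below) will be extracted from the stabilogram-diffusion analysis to describe different aspects of the postural control process". It continues: "These include two sets of the following parameters; one for medio-lateral and one for the anterior posterior direction and one resultant". Six types are then defined: critical time, critical displacement, and short- and long-term diffusion coefficients and scaling exponents. The same item adds: "Stabilogram-diffusion parameters will be extracted for both eyes-open and eyes-closed conditions". A further contrast follows: "The difference in critical displacement between eyes-open and eyes-closed will be used as an indicator of how much an individual relies on vision".

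**The analysis.** The Statistical analysis section lists all six types without selecting any: "postural stability measure (C_T_, C_D_, D_S_, D_L_, H_S_, H_L_), BBS, TUG, and LL-FDI scores will be calculated using SPSS". It sets the significance level at p<0.05. Where a variable shows a difference between the two training circuits, post hoc "comparisons with Bonferroni adjustment will be made".

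**The concern.** A hypothesis about balance control needs a test that can fail. Here it has many parameters, each compared with 0.05, and nothing says which of them decides the matter. The Bonferroni step starts only after a variable has shown a difference. It therefore limits errors among the follow-up comparisons for that variable and does nothing about the number of variables examined.

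The direction of benefit is also open. The definitions explain what each parameter reflects, but for critical time and the scaling exponents, for example, they do not say whether a rise or a fall is an improvement. A significant shift either way could then be presented as better control.

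At stake is the second of the two claims that the abstract promises to settle. An ineffective programme could yield some significant stabilogram result by chance, and the plan gives a reader no means of telling that result from a real effect.

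**Working it through.** **Inputs from the protocol article**
- Six parameter types (item 2 and Statistical analysis).
- Medio-lateral, anterior-posterior and resultant (item 2).
- Two vision conditions (item 2).
- Significance level 0.05 (Statistical analysis); two-sided, as stated for the sample size (Sample size estimate).

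**Assumed:** the correlations between parameters. The article gives none, so a range is shown.

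**1. The plan's own count.** 6 types × 3 = 18, which reproduces the stated eighteen. With both vision conditions, 18 × 2 = 36. This 36 is derived; the article does not state it. The same sentence speaks of two sets, which would give 6 × 2 = 12, or 24 with both vision conditions. The eyes-open versus eyes-closed contrast in critical displacement could add up to 3.

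**2. Independent tests, no true effect.** The chance of at least one significant result in either direction is 1 − 0.95^k. For a favourable result only, it is 1 − 0.975^k, since half of each two-sided 5% lies on that side.

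| Tests (k) | Either direction | Favourable only |
|---|---|---|
| 1 | 5.0% | 2.5% |
| 6 (types only) | 26.5% | 14.1% |
| 12 | 46.0% | 26.2% |
| 18 | 60.3% | 36.6% |
| 24 | 70.8% | 45.5% |
| 36 | 84.2% | 59.8% |

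The expected number of false significant results among 36 is 36 × 0.05 = 1.8.

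**3. Correlated tests, k = 36.** Multivariate normal simulation, 100,000 draws, critical value 1.96, equal correlation between all pairs. The simulation error is at most √(0.25/100,000) = 0.0016, about 0.2 percentage points.

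| Assumed correlation | Either direction | Favourable only |
|---|---|---|
| 0.3 | 72% | 38% |
| 0.5 | 55% | 28% |
| 0.7 | 36% | 18% |
| 0.9 | 18% | 9% |

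With correlation structured by type (0.3–0.5), sway direction (0.5–0.7) and vision condition (0.7–0.8), the results are 61–70% in either direction and 33–40% favourable.

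**4. Would a stricter informal rule help?** Requiring at least two of 36 significant results, if independent, gives 1 − 0.95^36 − 36 × 0.05 × 0.95^35 = 1 − 0.158 − 0.299 = 54% in either direction.

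**5. Bonferroni across all 36, as an alternative.** The per-test level is 0.05/36 = 0.00139, critical value 3.197. For illustration, take the article's effect size of 0.8 and 32/2 = 16 per arm, compared as parallel arms by the normal approximation: power = Φ(0.8 × √(16/2) − z).
- At 0.05: Φ(2.263 − 1.960) = 61.9%.
- At 0.00139: Φ(2.263 − 3.197) = 17.5%.

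Adjusting over all 36 is therefore expensive. A single parameter named in advance holds the error at 5% without that loss.

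**The case against.** The strongest reply is that these measures are not primary. The article names five primary outcomes, all from the voluntary step test. The sample size rests on foot-contact time, and the hypothesis in the Background concerns stepping only. Secondary, mechanistic measures are often left unadjusted, and their handling is commonly left to an analysis plan, which is not shown here. The article also describes the parameters as describing postural control. All of this stands as a limit on severity. It does not dispose of the point: the article itself states the level, lists the variables and says where Bonferroni applies, and its abstract and Discussion put balance control beside stepping speed. The rule is fixed badly rather than left open.

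Second, a reader might infer that one significant parameter out of 36 is the plan's criterion for success. The documents do not support that. No section says how many parameters must be significant, and the Berg Balance Scale and Get-Up-and-Go Test also bear on balance. The error rates above describe what an unspecified criterion permits.

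Third, 36 is one reading; 12, 24 or only the six listed types are others. This stands, and the table covers them. Six independent tests, counted only when favourable, still give 14.1%, against 2.5% for one such test.

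Fourth, the either-direction figures include results showing worse balance, and independence is not credible. Critical displacement is read at the critical time, the diffusion coefficients are slopes of the same plot, and the same people are tested under both vision conditions. This also stands, so the lower rows and the favourable column matter. The either-direction column keeps some relevance for parameters with no stated direction of benefit.

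**Conclusion.** The point holds as a defect in how the second headline claim is tested. With up to 36 parameters and no true effect, the chance of at least one significant result is 84% if independent and about 72%, 55% and 36% at correlations of 0.3, 0.5 and 0.7. For favourable results only, it is about 60%, 38%, 28% and 18%. These figures rest on the derived count of 36, on assumed equal correlations and on every null being true. The actual rate cannot be known from the article, but it is well above 5% at these correlations.

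A reader might go further and say that a false claim of improved balance is likely. That is too strong: among these equal-correlation figures, a false favourable result passes one half only under independence. Nor does the point touch the primary step outcomes, since no stabilogram parameter is among them. It should be corrected, but it does not undermine the trial's main comparison.

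**What to change.** Before unblinding, name one stabilogram parameter, in one sway direction and one vision condition, as the test of the balance-control hypothesis at 0.05, and state which direction of change is improvement. Medio-lateral critical displacement is one option. It fits the training target of medio-lateral stance control under Specificity and the definition of critical displacement as reflecting sway the subject can control. The choice is the sponsor's.

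Report every other stabilogram parameter as exploratory, with estimates and confidence intervals, and base no conclusion of improved balance on them alone. Reconcile the count in item 2, so that it is clear whether the resultant is a third set.

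If a single main step outcome is also chosen from the five, the balance test can follow it in a fixed sequence. That step is not available until the choice is made.

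The cost is a few lines of wording and no new data. The sponsor gives up claiming improved balance from whichever parameter happens to be significant.
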